## **15.2 Subset Calculation**

Within this phase II/III study, the Forced Expiratory Volume in 1 second ( $FEV_1$ ) at Week  $24 \pm 1$  week versus baseline was used as the primary efficacy endpoint. The efficacy of the investigational product Tigerase (GENERIUM JSC, Russia) will be compared with the efficacy of Pulmozyme® (F. Hoffmann-La Roche Ltd., Switzerland) in treatment of CF patients. However, since this disease is very rare, the number of patients available in Russia does not allow conducting a study using a generally accepted format of non-inferiority testing. In this regard, it is planned that the study will include all available patients aged 18 and older with an established diagnosis of cystic

fibrosis according to the relevant registries. According to preliminary information, up to 125 such patients can be available.

In this study, it is proposed to test the null hypothesis about the equality of efficacy of the two products,  $H_0: \Delta FEV_1$  (Tigerase) =  $\Delta FEV_1$  (Pulmozyme®), where  $\Delta FEV_1$  represents the change in Forced Expiratory Volume in 1 second (absolute %) on Week 24  $\pm$  1 week compared to baseline in the Tigerase and Pulmozyme® groups, respectively.

The alternative hypothesis is two-sided,  $H_a: \Delta FEV_1$  (Tigerase)  $\neq$   $\Delta FEV_1$  (Pulmozyme®). The null hypothesis will be tested using a two-tailed test at a significance level of 0.05 ( $Z_\alpha = 1.96$ ). The planned study power will be 80% ( $Z_\beta = 0.84$ ), which will allow detecting a difference ( $\delta$ ) of 5% or more between the compared groups for  $\Delta FEV_1$ , with the expected standard deviation of 10% for this parameter ( $\sigma$ ) (Table 3):

$$\delta^2 = \sqrt{\frac{4(Z_\alpha + Z_\beta)^2 \sigma^2}{n}}$$

**Table 3. Expected magnitude of differences for the primary efficacy endpoint ( $\Delta FEV_1$ ), which can be detected with the specified subset size**

| n | <math>\sigma</math> (%) | <math>\alpha</math>; 1-<math>\beta</math> (%) | <math>\delta</math> (%) |
|----------|--------------------------------|------------------------------------------------------|--------------------------------|
| 70       | 10                             | 0.05; 80                                             | 6.7                            |
| 80       | 10                             | 0.05; 80                                             | 6.3                            |
| 90       | 10                             | 0.05; 80                                             | 5.9                            |
| 100      | 10                             | 0.05; 80                                             | 5.6                            |

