| Statistical methods:             | 
The study was planned to test the null hypothesis of the equal efficacy of two medicinal products at W24 versus baseline in the compared groups. The sample size of 100 patients (the number of patients who could have been enrolled based on the feasibility result) was determined to allow to detect the difference (<math>\delta</math>) of 5% or more in <math>\Delta FEV_1</math> between the groups with the expected standard deviation (<math>\sigma</math>) of 10%, the power of 80% (<math>Z_\beta = 0.84</math>) and two-sided <math>\alpha = 0.05</math>.
 
The trial data were analyzed in three patient populations:
 
 
1) all patients included in the study (FAS population, full analyzes set); this population was also used as a baseline in the analysis of performance parameters;
 
2) all patients who received at least one dose of the study drug were included in the analysis of safety; the safety population was found to be identical to the FAS population;
 
3) additionally, the efficacy parameters were analyzed in all patients who completed the study without significant deviations from the Protocol (PP-population, Per protocol).
 
 
Descriptive statistics are given for each studied parameter. The two-sided t-test was used to analyze between-group differences for the primary efficacy endpoint in the intent-to treat population, in addition, a 95% confidence interval was provided.
 |

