## **1.7 Study Population**

The study will include male and female patients aged 18 and older with the confirmed diagnosis of cystic fibrosis with  $FEV_1 \geq 40\%$  and  $\leq 100\%$  of the proper value who meets all inclusion criteria described in detail in Section 4 of this Protocol.

The diagnosis of cystic fibrosis is defined as the presence of a clinical pattern of the disease in combination with a positive sweat test and/or detection of 2 gene mutations of cystic fibrosis

transmembrane regulator (CFTR) by genotype test (if there is a documented confirmation of cystic fibrosis diagnosis, these tests are not required).

The choice of this population was based on the evidence of pulmonary function improvement and reduced incidence and risk of infectious exacerbations from the clinical studies using dornase alfa in adult CF patients. [12, 71]

Enrollment into the study of the patients with  $FEV_1 \geq 40\%$  and  $\leq 100\%$  of the proper value is based on the data of numerous clinical studies that have demonstrated the efficacy of dornase alfa for the treatment of CF patients with mild to moderate pulmonary impairment. Inhalations of dornase alfa result in the reduction of sputum viscosity and surface adhesiveness in CF. Less viscous sputum is easier cleared away from the lungs with the help of mucociliary clearance and coughing, it improves the pulmonary function and reduces the rate of exacerbations in adult CF patients. The dornase alfa using is safe; the adverse reactions associated with its use are rare. [12, 19, 37–40, 51–52, 58, 69]

The expected number of screened patients is 125 people (including 20% exclusion during the screening).

Number of patients randomized: 100 patients.

Number of patients who completed the study: not less than 80 patients.

The patients will only be enrolled in the study if they have signed the Informed Consent Form, completed all screening procedures, and met all requirements of inclusion/exclusion criteria.

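### 100 patients do not give 80% power for a 5-point difference in ΔFEV1: Table 3 gives 5.6 points at 100, and power for 5 points is about 70%, or about 60% at the stated minimum of 80 completers

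*Protocol*

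**What the plan says.** The link between 100 patients and a 5% difference is explicit in the Protocol Summary, under Statistical methods: "The sample size of 100 patients (the number of patients who could have been enrolled based on the feasibility result) was determined" so that a difference of 5% or more in ΔFEV1 could be detected. The inputs given there are an SD of 10%, 80% power and a two-sided level of 0.05.

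Protocol section 15.2 repeats the inputs: a "two-tailed test at a significance level of 0.05", "The planned study power will be 80" per cent, a difference "of 5% or more between the compared groups", "with the expected standard deviation of 10% for this parameter". It refers to Table 3 for the result. Table 3 lists detectable differences of 6.7, 6.3, 5.9 and 5.6 for n = 70, 80, 90 and 100, with SD 10, level 0.05 and power 80% in every row.

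On numbers, section 1.7 plans 125 screened and 100 randomised, and adds: "Number of patients who completed the study: not less than 80 patients". Section 15.1 makes the primary comparison an unadjusted t-test, or a Mann–Whitney test if normality fails, with a 95% confidence interval for the group difference.

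**The concern.** The sentence and the table it cites give different answers from the same inputs: 5 in the text, 5.6 in the table at the number to be randomised. The difference that the table allows at the minimum number of completers is larger again.

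The design makes this figure matter. Section 15.2 says that a conventional non-inferiority test is not feasible, and it tests equality of a biosimilar with its reference product. In such a trial a non-significant result is the one that favours the new product, and how much weight it carries depends partly on the chance of detecting a relevant difference. If power for 5 points is stated as 80% but is 60% to 70%, the chance of missing a true 5-point difference is understated: it is 30% to 40%, not 20%.

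**Working it through.** **Inputs, all from section 15.2 and the Summary.** Zα = 1.96 (two-sided 0.05), Zβ = 0.84 (80% power), σ = 10, δ = 5. Allocation is 1:1 (section 3.2), so n is the total over two equal groups. The n values of interest are 100 (randomised) and 80 (minimum completers).

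**Step 1: reproduce Table 3.** For two equal groups with total n,

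δ = √(4(Zα + Zβ)²σ²/n) = √(4 × 2.8² × 100/n) = √(3136/n).

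| n | δ computed | δ in Table 3 |
|---|---|---|
| 70 | 6.69 | 6.7 |
| 80 | 6.26 | 6.3 |
| 90 | 5.90 | 5.9 |
| 100 | 5.60 | 5.6 |

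Every row reproduces. This confirms that n is the total sample and that the table is correct.

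**Step 2: try to reproduce the sentence.** Solving for n at δ = 5 gives 3136/25 = 125.4. That is 63 per group, 126 in all; the noncentral t calculation gives 128. So 5% at 80% power is not obtained at 100.

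**Step 3: power for δ = 5.** By the normal approximation, power = Φ(δ/(σ√(4/n)) − 1.96).

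- n = 100: 5/(10 × 0.2) = 2.50, and Φ(0.54) = 70.5%. The t-test gives 69.7%.
- n = 80: 5/(10 × 0.2236) = 2.24, and Φ(0.28) = about 60.9%. The t-test gives 59.8%.

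**Step 4: look for a reading that rescues the sentence.**

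- A one-sided 0.05 test gives 80.4% at n = 100, but the plan specifies a two-tailed test with Zα = 1.96.
- A smaller SD would do it: 8.9 at n = 100 (5 × 10/5.6) or 8.0 at n = 80 (5 × √80/5.6). The plan states 10.
- Covariate adjustment would have to remove about 20% of the variance at n = 100 (1 − 0.893² = 0.20). The primary test is unadjusted, and the generalized linear model in section 15.1 is optional.

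**Step 5: the printed formula.** It shows δ² on the left and a square root on the right. Read literally it gives δ = √5.6 = 2.37 at n = 100, which is not what Table 3 shows. With the square removed it matches the table.

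**The case against.** Several points on the other side are fair.

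- **The sample size was set by feasibility.** The Summary says so and section 15.2 explains why. The correct detectable differences are printed directly below the sentence in 15.2. This stands: correcting the text alters no enrolment figure, test or decision rule. It does not make the sentence true, and the Summary carries no table to correct it.
- **Section 15.2 does not itself tie 5% to 100 patients.** This also stands. Only the Summary makes that link. The conflict within 15.2 is narrower: it cites a table in which no row reaches 5.
- **80 is a floor.** A reader might infer that the true power is 60% because 80 patients are expected. The documents do not support that. The plan says not less than 80, section 15.1 assesses primary efficacy in all treated patients by intention to treat, and section 9.8 schedules spirometry at an early termination visit. How those values enter the Week 24 analysis may be settled in the statistical analysis plan. The evaluable number therefore lies somewhere from 80 to 100, and 60% is the lower end.
- **Power does not decide what a result excludes.** A reader might infer that a non-significant result would be taken to rule out a 5-point loss. The plan also provides a 95% confidence interval for the difference, and that interval shows what is excluded whatever power was stated.
- **The origin of the 5% is unknown.** The formula gives 5.01 at n = 125, the number to be screened and the upper limit of available patients. A reader might infer that the wrong n was used. The arithmetic coincides, but the protocol does not say so.

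**Conclusion.** The stated power is wrong as written. At the plan's own SD of 10%, two-sided 0.05 level and 1:1 allocation, 100 evaluable patients give 80% power for 5.6 points, not 5. Power for 5 points is about 70% at 100 evaluable patients and about 60% at the minimum of 80, so the shortfall against the stated 80% is about 10 to 20 percentage points. Eighty per cent power for 5 points would need about 126 evaluable patients, which is slightly more than the 125 that the plan believes to be available.

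These figures assume a t-test on approximately normal changes and that the SD of 10% is right. The protocol gives no other SD.

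Two stronger readings go too far. The stray square in the formula does not undermine Table 3, since every entry is correct; it is a misprint. Nor does the point show that the trial must enrol more patients, because its size rests on availability. What has to change is the claim made for that size.

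**What to change.** In the Summary (Statistical methods) and in section 15.2, replace the 5% figure by a detectable difference of 5.6% with 100 evaluable patients, rising to 6.3% if only the minimum of 80 are evaluable, each at 80% power. Add that the power for a 5% difference is about 70% with 100 evaluable patients and about 60% at that minimum. Keep Table 3 as it is.

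As a typographical correction, remove the square on δ so that the formula reads δ = √(4(Zα + Zβ)²σ²/n).

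The cost is wording in two places and one symbol. Enrolment, the primary test and the confidence interval do not change. The stated sensitivity of the trial becomes less favourable, but it then agrees with the plan's own table.

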### 15.3 Deviation from the Statistical Data Analysis Plan

The statistical data analysis plan will be compiled and approved before the database lock. The statistical data analysis plan will contain a detailed description of cumulative data compilation and data analysis procedure (primary analysis and subanalysis), as well as clear scheduling of these kinds of analysis. All deviations from the initial statistical data analysis plan will be described and substantiated in the Clinical Study Report.

### 15.4 Adverse Events

The data on adverse events will be encoded using the current version of the MedDRA medical dictionary. The incidence of adverse events during treatment will be calculated for each organ system, according to the main diagnosis, treatment group, and in terms of the absolute and relative number of patients who developed adverse events. Summary data on the severity of adverse events and their relationship with the treatment will be presented for each organ system and by the principal diagnosis.

The cumulative data on the withdrawal of patients due to adverse events will be provided for each organ system and by the principal diagnosis.

The data on serious adverse events will be presented as lists and as cumulative data for each organ system and by the principal diagnosis.

## **16 SOURCE DATA, DATA HANDLING, MAINTENANCE, ARCHIVING, AND RECORD RETENTION**

### **Sources and access to source data, data handling, documentation maintenance**

As the subjects undergo scheduled visits and the investigators fill out the CRFs, the Sponsor's authorized monitor will verify the CRFs and the source documentation.

The study should be conducted in accordance with the Protocol and standard operating procedures of the Sponsor. If amendments to the Protocol are required, the Investigator and the Sponsor should agree on these amendments and document them as an amendment to the Protocol subject to the approval by the Ethics Committee.

All investigators are required to fill out the basic documentation of the clinical study — the original medical records and the CRFs.

The Investigator is responsible for the complete and accurate filling of the CRFs. All data recorded in the CRFs should also be included in the original medical records of a subject in printed form or in the form of records made by the Investigator or another authorized person at the clinical center.

In accordance with the source documentation, all proposed data on the participation of a subject in the study should be recorded in the CRFs. The CRFs should also contain the data regarding the subject's completion of participation in the study. The CRFs shall be filled out not later than 5 days after the subject's visit to the study center.

All missing data in the source documentation and in the CRFs should be supported with an explanation in the form of comments. The CRFs should be signed by the Principal Investigator. These signatures verify reliability of the information presented in the CRF.

The Investigator is obliged to provide direct access to the subject's data and study records when conducting study-related monitoring, audit, and inspection by the authorized regulatory bodies and to give all necessary explanations to the representatives of these organizations.

All information on the study and collected data are strictly confidential. The Investigator is only entitled to provide information on the study to persons not directly involved in it with the Sponsor's permission.

The Final Report consisting of a statistical and clinical report is formed after the database lock date and completion of the statistical processing of the study data. The Final Report should be signed by the Principal Investigator of the clinical center, who confirms the results and conclusions of the study attaching it with this organization's seal.

## **16.1 Record Archiving and Retention**

At the clinical center, all records and documents related to the clinical study and contained in the Investigator's file, including informed consent forms, logs, subject registries, as well as the subject's source medical records must be kept for 15 years after completion of the study. The study Sponsor provides retention of all materials of the clinical study throughout the entire life cycle of the investigational product.

Archival data can be stored as photocopies or on optical/electronic storage media. The Principal Investigator of the clinical center is obliged to immediately inform the Sponsor about the destruction or changes in the location of the archived materials of the clinical study.

## **17 ETHICAL ASPECTS OF THE STUDY**

### **17.1 General Provisions**

This study will be conducted in accordance with the Declaration of Helsinki of the World Medical Association, Ethical Principles for Medical Research Involving Human Subjects, dated 1964, with subsequent amendments and additions; National Standard of the Russian Federation GOST R 52379-2005, Good Clinical Practice, dated September 25, 2005, Federal Law of the Russian Federation No. 61-FL, On Circulation of Medicines (with subsequent amendments and supplements), dated April 12, 2010, as well as guidelines of the International Conference on Harmonization — Good Clinical Practice (ICH GCP).

### **17.2 Procedure for Informed Consent Obtaining**

Prior to enrollment into the study, the subject should be provided with a written or oral explanation of the purposes, objectives, and methods of the study, as well as expected benefit and potential risk associated with the participation in the study. In addition, the subjects should be informed about the voluntary nature of participation in the study and that the subject has a right to withdraw from the study at any time, and that such withdrawal will not affect the quality of the medical care provided to him/her. Although the subject is under no obligation to report the reasons for his/her withdrawal, the Investigator should try to find them out, however, without prejudice to the subject's rights. The subject's consent should be obtained prior to any study procedures.

Processing of the data collected during the study should be performed while maintaining the confidentiality of the subjects' data. The subjects should be informed about the purposes of the planned computer processing of the data and terms of these data publication (for example, for presentation at medical conferences, in journal articles, and other publicly available sources), presented only in the aggregated form that does not allow any identification of the subject.

Subjects should be informed that authorized representatives of healthcare authorities and the Sponsor will have access to their confidential medical information for monitoring, inspection, and audit. Subjects are guaranteed strict confidentiality of all information that allows identifying the subject, and non-disclosure of such information. The Informed Consent Form (Patient Information Leaflet) shall be filled out in duplicate, signed, and dated by the subject and the Investigator in their own hand. The Investigator should keep one copy of the signed Informed Consent Form in the Investigator's File, and the other copy is handed over to the subject.

### **17.3 Study Subjects Confidentiality and Identification**

The confidentiality of identifiable records will be maintained in accordance with the right to privacy and confidentiality in accordance with regulatory requirements. Personally identifiable records will be protected and kept confidential and may only be disclosed to the extent it is allowed by the legislation. If the study results are published, the confidentiality of the information regarding the subjects' data will be preserved.

### **17.4 Recruitment of Subjects from Specific and Vulnerable Populations**

The criteria of inclusion/exclusion stipulate participation in the study of the women with preserved childbearing potential if they provide consent for the use of reliable contraception methods specified in Section 4.2.

## **18 STUDY MONITORING AND STUDY QUALITY ASSURANCE**

Regular visits of the study monitor before, during the study, and upon the study completion contribute to the success of the study and serve as a guarantee for collecting accurate data, timely detection of possible errors, documenting the clinical study process, and ensuring the protection of the rights of study subjects and compliance of the study with the requirements of international and Russian laws.

Routine monitoring of the study includes:

- Confirmation of proper study conduct and documenting the process of obtaining informed consent, as well as screening and enrollment of subjects in the study;
- Verification of the CRF data and source medical records of the study subjects;
- Confirmation of documenting and timely reporting of AE data during the study; confirmation of the clinical center personnel's compliance with the requirements for the implementation of diagnostic and therapeutic procedures of the study protocol;
- Confirmation of documenting the supply, storage, distribution, and destruction of the investigational product/study materials;
- Confirmation of the competence of the clinical center personnel and external laboratory personnel required for the study;
- Confirmation of the compliance of diagnostic and laboratory equipment with the requirements for their safe and adequate use during the study;
- Confirmation of the Investigator's cooperation with the local ethics committee on questions pertaining to the study safety and making amendments to the study protocol agreed by the Sponsor.

In accordance with legal requirements, the Sponsor or authorized state bodies have the right to inspect (audit) the study materials and equipment as well as the study records. The Investigator should provide access to the documentation and all the necessary information to those authorized to conduct an audit or inspection.

## **19 PROTOCOL AMENDMENT, DEVIATION, AND VIOLATION**

Investigators' signatures on the signature page of the protocol constitute written confirmation of agreement to conduct the study in accordance with this protocol. Amendments and supplements may be introduced into the study materials during the clinical study. Such changes and supplements should be considered as amendments.

Protocol amendment means a written description of changes or a formal explanation of the text of the clinical study protocol. Amendments can be significant and minor. Prior to entry into force, each protocol amendment should be approved in accordance with the established internal standard operating procedures of the Sponsor, after which it is approved by the Ministry of Health of the Russian Federation and local ethics committees and signed by the Investigator.

Order of the Ministry of Health of the Russian Federation No. 775 dated August 31, 2010, On Approval of the Procedure for Processing the Statement about the Need to amend the Clinical Study Protocol of the Medicinal Product, defines the list of significant/minor amendments and the procedure for the relevant materials submission for expert examination.

Amendments to clinical study materials should be considered significant if they may affect the purposes, forms of management, methodology of conduct, statistical methods of processing the clinical study results, and measures to ensure the safety of the patients participating in the study.

Amendments to clinical study materials should be considered minor if they do not affect the purposes, forms of management, methodology of conduct, statistical methods of processing the clinical study results, and measures to ensure the safety of the patients participating in the study.

If there is a need to amend this protocol, the Sponsor sends a notification of the need to amend the clinical study protocol to the Ministry of Health of the Russian Federation. The decision to make changes or refuse to make changes is made by the Ministry of Health of the Russian Federation after an examination of the updated materials submitted.

Protocol amendments should be stored along with the initial protocol version. The number of the amendment and its effective date should be indicated on the title page of the protocol. All deviations from the Protocol during the study should be documented during the monitoring of the clinical study.

